**Fig. 2 Fig2:**
[figure not shown]
*Flow chart* of study design

### Blinding

Patients will remain blinded regarding the category of their allocation throughout the study data collection period. Additionally, the evaluators responsible for the data collection and the outcomes assessor will also be blinded to the patient allocation. The acupuncturist responsible for the interventions will be the only person not blind to the type of treatment to be performed.

### Qualification of practitioners

The interventions will be performed by acupuncture specialists with at least three years of clinical experience, who will receive prior training to ensure that they rigorously follow the study protocol and are familiar with the types of treatments, including details such as acupuncture points and manipulation of electroacupuncture parameters.

### Outcome measures

Four stages of evaluations will be performed: (1) before the start of treatment; (2) immediately after the end of treatment (five weeks); (3) at six months; and (4) one year after the final treatment. The evaluators will be trained in advance.

The primary clinical outcome will be pain intensity. The secondary outcomes will include quality of pain, physical functioning, perception of overall effect, emotional functionality, patient satisfaction, and psychosocial factors. All the scales and questionnaires have been translated into Brazilian Portuguese, with the exception of the visual analog scale for the assessment of anxiety, and their properties clinimetrically tested [13–16].

### Primary outcomes

#### Pain intensity

##### Numerical rating scale (NRS)

The NRS is an 11-point scale ranging from 0 (no pain) to 10 (worst possible pain). Participants will be asked to rate their average pain levels in the 24 h before the assessment [17].

The pressure pain threshold (PPT) will be measured using a pressure algometer (EMG System, Brazil). The assessed region will be marked with a tape measure and a dermatographic pencil. Two points will be marked bilaterally: 5 cm to the right and left of the spinous process of L3 and L5. A control point will be marked on the anterior tibial muscle of the right leg, 5 cm lateral to the tuberosity of the tibia [18]. The circular tip of the algometer will be positioned perpendicular to the participant’s skin and gradually pressed until the participant reports that the pressure has become painful and unbearable. Three measurements will be taken at each point with an interval of 1 min. Finally, the arithmetic mean will be used to define the pressure pain threshold [18].

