### Sample size

Based on a previous study [11], the sample size was calculated to detect a difference of 2 points on the pain intensity measured by the 11-point pain NRS. In our study, the sample size was calculated using the program G*Power 3 3.1. 9.2, with an estimated standard deviation of 1.47 points [30], a moderate effect size (0.35) [31], a statistical power of 80% (1 β error probability), and an α error level probability of 0.05. The study will require 105 individuals. However, an extra 20% of participants will be added in order to increase the power. Thus, this study will therefore require a total of 125 participants, with 25 in each group.

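### The algometry outcome is named a pressure pain threshold but is read at an unbearable-pressure end point, so name and stopping rule do not match

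*Protocol article*

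**What the plan says.** In the protocol article, the section Primary outcomes, under Pain intensity, describes two measures: the 11-point NRS and pressure algometry. On the second it says: "The pressure pain threshold (PPT) will be measured using a pressure algometer". Pressure is applied at four lumbar points (both sides at L3 and L5) and at one control point over the right anterior tibial muscle. At each point the tip is "gradually pressed until the participant reports that the pressure has become painful and unbearable". Three readings are taken per point, and "the arithmetic mean will be used to define the pressure pain threshold".

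The Outcome measures section states: "The primary clinical outcome will be pain intensity". Its list of secondary outcomes leaves algometry out: "The secondary outcomes will include quality of pain, physical functioning, perception of overall effect, emotional functionality, patient satisfaction, and psychosocial factors". The Sample size section is built on the NRS alone; it aims to "detect a difference of 2 points on the pain intensity measured by the 11-point pain NRS" and uses "an estimated standard deviation of 1.47 points".

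No other section gives a different stopping rule for the algometer, and none mentions pressure tolerance.

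**The concern.** A pain threshold and a pain tolerance are different quantities. The first is the pressure at which the sensation turns painful; the second is the most pressure a person will accept. The article uses the name of the first and the stopping rule of the second.

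Two consequences follow. First, interpretation: a reader who sees a treatment effect on the pressure pain threshold will take it as a change in when pain begins, and may compare the values with threshold data from elsewhere. Neither use is justified if the readings were taken at the unbearable point. Second, consistency: the instruction names two sensations, painful and unbearable, that occur at different pressures. If some evaluators or participants stop at one and some at the other, the outcome mixes two quantities and carries extra variation.

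The placement adds weight, because the measure sits under the primary outcomes heading.

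**Working it through.** **1. Name against stopping rule.** The check is mainly one of reading.

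| Element | What the article says | What it implies |
|---|---|---|
| Name | Pressure pain threshold | First pain |
| Stopping rule | Pressure both painful and unbearable | Both conditions must hold, so the later one governs: tolerance |
| Recorded value | Mean of three such readings per point, reported as the threshold | A tolerance value under a threshold name |

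**2. What the recorded value estimates.** Let T be a participant's threshold, L the tolerance, and G = L − T, which is zero or more by definition.

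- Stopping rule followed literally: the reading is L = T + G. The difference between arms is then (difference in T) + (difference in G). It equals the difference in threshold only if treatment leaves G unchanged, and nothing in the article establishes that.
- Stopping point varies: the reading is T + sG, with s between 0 and 1 depending on the evaluator, participant or visit. Variation in s adds noise that averaging three readings need not remove, because s can be shared by all three.

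The article gives no value for G, its variance or s, so neither the shift nor the noise can be put in figures.

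**3. Does it reach the NRS or the sample size?** Inputs from Sample size: effect size 0.35, power 80%, alpha 0.05, N = 105, raised to 125 in five arms. I assumed that 0.35 is Cohen's f and that the test is the one-way omnibus F test, with noncentrality λ = N × f².

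- At N = 105: λ = 105 × 0.35² = 105 × 0.1225 = 12.86; power 0.812. The smallest N reaching 80% is 103, or 105 with equal arms of 21, so the article's figure reproduces.
- At N = 125: λ = 125 × 0.1225 = 15.31; power 0.885.

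No algometry quantity enters, so rewording that outcome changes none of these figures.

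**4. Number of presses.** Four lumbar points + one tibial point = 5; 5 × 3 readings = 15 per visit; 15 × 4 visits = 60. This count is the same under any stopping rule, so it does not measure the mismatch. It matters only if evaluators do press to the unbearable point. In that case up to 60 readings per participant, aged 60 or older, go further than a threshold requires.

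**5. How much may already have been measured.** Trial status gives recruitment from April to October 2019, and the article was published on 23 December 2019. If recruitment kept to schedule and treatment began promptly, the last five-week course would end in early December 2019. Baseline and most post-treatment readings would then precede publication, with most follow-up readings at six months and all at one year still to come. A change of instruction at that stage would fall between visits of the same participant.

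**The case against.** The strongest reply is that this is a slip of wording. The procedure cites a source that is not shown, the evaluators' own script is not shown either and may be in another language, and evaluators are trained in advance and blinded. They may well stop at first pain. This stands in part: the article does not establish what is done in practice, and any statement about burden must stay conditional. It does not remove the point, because the published operational definition conflicts with the outcome's name and nothing else in the article corrects it.

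A second reply is that the same instruction applies in all five arms, so a tolerance reading taken uniformly can still be compared between arms. This stands. The remaining problem is then the label and its interpretation, not bias between arms.

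A third is that primary status rests on a heading only: the Abstract and Outcome measures name pain intensity, and the trial is sized on the NRS. That limits the reach of the point. Still, the measure is described under the primary heading and is absent from the secondary list.

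A reader might also infer that the mean pools the lumbar points with the tibial control, diluting a lumbar effect by one fifth. The article does not support this. The sentence just before the averaging rule says that three readings are taken at each point, so a mean per point is the natural reading, and the tibial site is expressly a control. The one-fifth figure would also need no effect at the leg, although the Procedures and Interventions sections place needles at leg acupoints (BL40, SP6, KI3).

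**Conclusion.** The mismatch is real. A measure placed under the primary outcomes is named a threshold but defined by a tolerance end point, or at best by an ambiguous pair of end points. Reported as planned, it would be misread as first-pain threshold.

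Its size is unknown. By definition a tolerance reading lies at or above the threshold, but the documents do not say by how much. The conclusion rests on the ordinary meaning of the two terms and on the instruction being used as printed.

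It would go too far to infer that the trial's main result is compromised, that the arms are compared unfairly, or that participants are in fact pressed to unbearable pain. The NRS outcome and the sample size stand apart from this text, the instruction is common to all arms, and actual practice is not documented. The point is a correction worth making, not a threat to the trial.

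**What to change.** First establish, from the evaluators' script and training material, which end point has been used. Then reconcile name and rule:

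- **If first pain was used:** keep the name and correct the sentence so that participants signal when the pressure first becomes painful. No data change.
- **If the unbearable point was used:** keep that one instruction at all four visits for participants already measured, and rename, analyse and interpret the outcome as pressure pain tolerance.
- **If practice varied:** identify which readings were taken under which instruction and do not pool them.

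In no case should the instruction change within a participant. The planned mixed model with treatment-by-time terms would otherwise confound change over time with a change of construct.

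The cost is a sentence in the protocol, a check of evaluator practice and a matching line in training. The downside is that the outcome may have to be relabelled, with loss of comparability with threshold data, and that some readings may be unusable together if instructions differed.

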### Secondary outcomes

#### Quality of pain

This will be analyzed using the McGill Pain Questionnaire, a valid and reliable instrument containing 78 pain descriptors divided into four categories (sensory, affective, evaluative, and miscellaneous) and 20 subcategories, to which scores of 1–5 are attributed [19, 20]. The result is obtained by first scoring the words according to their position within the set of descriptors of each subcategory. The maximum score in the sensory category is 42, in the affective 14, in the evaluative 5, and in the miscellaneous 17. The analysis is then performed by adding these values associated with their categories. Higher scores equate to more intense pain [19, 20].

#### Physical functioning

This measure will be assessed through the Roland Morris Disability Questionnaire (RMQ) and the Five Times Sit to Stand Test (FTSST).

RMQ is the Roland Morris Disability Questionnaire. It is a self-administered questionnaire, adapted to Brazilian Portuguese, which aims to evaluate physical incapacity due to LBP [13]. This contains 24 items pertaining to activities that can be impaired due to LBP. Individuals need to select the items that apply to their pain on that day. The selected items are summed for a total score ranging from 0 to 24, with higher scores indicating more severe functional incapacity

The activity of sitting and standing is a common and important movement in daily life; in clinical practice it helps to determine a person’s functional level [21]. The patient initiates the FTSST sitting in a chair without arm support, with the upper limbs crossed over the chest, feet positioned at hip width and knees in 90° flexion. They will be asked to stand and sit five times as fast as possible. A timer will be used to measure the task execution time. The test will be performed twice and the mean time will be calculated.

#### Perceived overall effect

The patient’s treatment self-perception will be evaluated using the Global Effect Perception Scale, an 11-point numerical scale ranging from − 5 (much worse) to + 5 (much better), where higher scores represent better recovery [17].

#### Emotional functionality

Depression and anxiety will be assessed using the Beck Depression Inventory (BDI) [14, 22] and the Global Anxiety - Visual Analog Scale (GA-VAS) [23], respectively.

The BDI is a self-administered questionnaire that contains 21 items, with a score in the range of 0–3, where a higher score indicates more depressive symptoms. The GA-VAS is composed of a 100-mm line, where the left extremity is related to the absence of anxiety and the right extremity is related to the worst possible anxiety. The individual is asked to assess the intensity of their anxiety in the previous 24 h and to mark this on the line. The distance from the left edge of the line to the mark placed by the patient is measured in millimeters. Greater measurements indicate greater anxiety.

#### Patient satisfaction

The evaluation of the patient’s treatment satisfaction will be carried out using the MedRisk questionnaire of patient satisfaction with physiotherapeutic care [15].

This questionnaire contains 20 items, covering global aspects of the treatment (two items), aspects related to the service provided (eight items), and aspects about the therapist–patient relationship (10 items). Following a Likert-type scale, the patient’s response will range from 1 (strongly disagree) to 5 (strongly agree), where higher scores represent greater satisfaction with the treatment.

#### Psychosocial factors

The risk of poor prognosis due to psychosocial factors will be assessed using the STarT Back Screening Tool (SBST), a self-administered questionnaire with nine items (four related to referred pain and five related to psychosocial factors), where the patient has the following response options: “I agree” (1 point) and “I Disagree” (zero points) for the first eight items; and “Nothing,” “A little,” or “Moderate” (zero points each), “A lot” or “Extremely” (1 point each) for the ninth item [16]. If the total score is in the range of 0–3 points, the patient is classified as low risk for poor prognosis. If the total score is > 3 points, the score of the psychosocial subscale, questions 5–9, is then considered. If the score of this subscale is ≤ 3 points, the patient is classified as medium risk and scores > 3 points are considered to indicate a high risk for poor prognosis [16].

### Procedures

After randomization, the acupuncturist will sequentially open the envelopes and the individuals will be randomly assigned to one of five treatment groups, each containing 25 participants: low frequency EA (LF); high frequency EA (HF); alternating frequency EA (AF); control group (C); and placebo group (P). The acupuncture points will be located and described according to the WHO Standard Acupuncture Locations [24]. Based on the beneficial effects of previous clinical trials, the acupoints selected for this study will be: BL23, BL25, BL40, SP6, and KI3 [10, 25–27] (Table 1).

**Table 1 Tab1:** Protocol for acupoints

Acupoints	Location
BL23 (Shenshu)	In the lumbar region, at the same level as the inferior border of the spinous process of the second lumbar vertebra (L2). 1.5 B-cun lateral to the posterior median line.
BL25 (Dachangshu)	In the lumbar region, at the same level as the inferior border of the spinous process of the fourth lumbar vertebra (L4). 1.5 B-cun lateral to the posterior median line.
BL40 (Weizhong)	On the posterior aspect of the knee, at the midpoint of the popliteal crease.
SP6 (Sanyinjiao)	On the tibial aspect of the leg, posterior to the medial border of the tibia, 3 B-cun superior to the prominence of the medial malleolus.
KI3 (Taixi)	On the posteromedial aspect of the ankle, in the depression between the prominence of the medial malleolus and the calcaneal tendon.

*BL* bladder, *SP* spleen, *KI* kidney

### Interventions

Participants of the LF, HF, and AF groups will be submitted to the treatment protocol, which will consist of the bilateral application of electroacupuncture using a previously calibrated electrostimulator (Sikuro DS100C), consisted of alternating symmetrical biphasic waves with continuous pulse train for the low (2 Hz) or high (100 Hz) frequency groups, and a mixed pulse train for the alternating frequency group (100 Hz and 2 Hz for 3 s each); 100 ms pulse duration and 0.5 ms pulse width; and the maximum current (amplitude) intensity tolerated by the patient and intensified so that sensory habituation is avoided. Trichotomy will be carried out when necessary and the skin will be disinfected with 70% alcohol. With the participant lying down in a ventral position, the needles will be inserted at a 90° inclination with the skin, to a depth at which that the patient reports the “deQi” sensation (≅ 1.5 cm). The protocol sessions will happen twice a week (30 min per session) for five weeks, at no cost to the participants.

Sterile and disposable 0.25 × 30 mm stainless-steel needles (Dong Bang Acupuncture Inc., Seoul, Republic of Korea) will be used. The sessions will last 30 min, twice a week, for five weeks, totaling 10 sessions [10, 26].

The individuals that are randomly assigned to the C and P groups will follow exactly the same protocol as the electroacupuncture groups; however, the C group will not undergo electrical stimulation, as the acupuncturist will activate channels that are not connected to the patient. In the P group, an adhesive moxa (Dong Yang®) will be placed on each acupoint and the needle will be inserted over it, so that the participant only feels the needle prick, but without perforation of the skin and the “deQi” sensation. In addition, as in group C, the electrodes will be connected to the needles; however, no electrical current will be applied [28].

### Placebo effect

The individuals will be instructed since recruitment that this research has five groups with different types of treatment. However, to ensure the blinding of the participants and to avoid biases in measuring outcomes [11], they only will be enlightened about the control and placebo group when they finish the 12-month follow-up evaluation. Also, in the post-treatment evaluation, each one of them will be asked to answer the questions: “Did you feel the needle penetrate your skin?” and “Did you feel that you received real electroacupuncture?”

The percentage of yes and no answers will be analyzed. A significant percentage of “no” responses may suggest that the placebo effect was insufficient. According to Research Ethics Committee of the Medical School of University of São Paulo and Resolution 466/2012 of the Brazilian National Health Council [29], if we observe that the therapeutic effect of one group (EA treatment or control) will statistically greater than the placebo group, we will ensure that all participants of this group receive the best treatment when they finish the 12-month follow-up evaluation.

### Adverse events

At each treatment session, the participants will be asked about any unpleasant and unintended signs or symptoms associated with the use of electroacupuncture. A questionnaire will also be used with a record of the duration and intensity of the adverse symptom reported by the patient, which will be scored according to a Likert-type scale of 1–5, with 1 representing the absence of adverse symptoms and 5 severe adverse symptoms. The severe adverse symptoms will exclude the participant from the treatment and the participant will be referred for medical consultation.

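### The adverse event question is limited to symptoms linked to electroacupuncture, although two of the five arms receive no current

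*Protocol article*

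**What the plan says.** Under Adverse events, the article fixes when participants are asked and what they are asked about: "At each treatment session, the participants will be asked about any unpleasant and unintended signs or symptoms associated with the use of electroacupuncture". It adds a second instrument, without saying when it is completed: "A questionnaire will also be used with a record of the duration and intensity of the adverse symptom reported by the patient".

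Under Interventions, the LF, HF and AF arms receive current at the highest intensity each patient tolerates, increased so that the sensation does not fade. For the acupuncture control, "the C group will not undergo electrical stimulation, as the acupuncturist will activate channels that are not connected to the patient". The placebo arm has needles that do not pierce the skin, with electrodes attached but no current. Treatment is short: "The sessions will last 30 min, twice a week, for five weeks, totaling 10 sessions".

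Under Outcome measures, the evaluations after baseline are "2) immediately after the end of treatment (five weeks); (3) at six months; and (4) one year after the final treatment". Adverse events are not among the outcomes listed for them: "The secondary outcomes will include quality of pain, physical functioning, perception of overall effect, emotional functionality, patient satisfaction, and psychosocial factors".

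Three other sections bear on the point. Blinding keeps patients unaware of their allocation throughout data collection. Placebo effect says participants know there are five different treatments, and has them asked after treatment whether they felt the needle go in and whether they felt they had received real electroacupuncture. Dropouts has reasons for withdrawal recorded over the whole study.

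**The concern.** A safety record is comparable across arms only if the same symptom has the same chance of being written down in each. Here the enquiry carries a causal condition: a symptom counts if it is associated with electroacupuncture. Someone has to make that judgement before anything is recorded, and the article does not say who. If it is the participant, the answer depends on what treatment the participant thinks is being given. Those in the electroacupuncture arms can feel the current; those in the control and placebo arms receive none.

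Two things are at stake. Symptoms nobody connects with the treatment go unrecorded in every arm, in a population aged 60 or over. Also, a difference in reports between arms could reflect perceived treatment as well as real events, and the record could not separate the two. A symptom never recorded cannot be recovered at analysis, so this has to be settled during data collection.

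Timing is a lesser matter. A delayed reaction to any of the first nine sessions can be picked up at the next one. Session 10 has no next session, and the article names no later occasion on which the question is put.

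**Working it through.** The plan gives no adverse event rate or safety calculation, so there is no figure of its own to reproduce. The sample size calculation does not enter.

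**Step 1. Who is asked a question that does not fit their treatment.** Procedures gives five arms of 25.
- With current: 3 × 25 = 75.
- Without current: 2 × 25 = 50, which is 50/125 = 40% of participants.

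**Step 2. What unequal attribution could do.** This step is illustrative and rests on assumptions. Let *p* be the true risk of a symptom, equal in all arms. Let electroacupuncture participants report all such symptoms, and let participants without current report a fraction *r* of them. Then:
- Spurious excess in the electroacupuncture arms = *p* − *pr* = *p*(1 − *r*).
- Apparent risk ratio = *p*/(*pr*) = 1/*r*.
- Expected reports: 75*p* with current, 50*pr* without.

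| *p* | *r* | Reports, 75 with current | Reports, 50 without | Excess (points) | Ratio |
|---|---|---|---|---|---|
| 10% | 1 | 7.5 | 5.0 | 0 | 1.00 |
| 10% | 0.75 | 7.5 | 3.75 | 2.5 | 1.33 |
| 10% | 0.50 | 7.5 | 2.5 | 5.0 | 2.00 |
| 10% | 0.25 | 7.5 | 1.25 | 7.5 | 4.00 |
| 20% | 0.75 | 15.0 | 7.5 | 5.0 | 1.33 |
| 20% | 0.50 | 15.0 | 5.0 | 10.0 | 2.00 |
| 20% | 0.25 | 15.0 | 2.5 | 15.0 | 4.00 |
| 30% | 0.75 | 22.5 | 11.25 | 7.5 | 1.33 |
| 30% | 0.50 | 22.5 | 7.5 | 15.0 | 2.00 |
| 30% | 0.25 | 22.5 | 3.75 | 22.5 | 4.00 |

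With *r* = 1 the excess is zero at every *p*. The documents give neither *p* nor *r*, so the table shows a range and is not an estimate.

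**Step 3. Whether the second instrument removes the filter.** The questionnaire records how long and how intense the symptom reported by the patient was. Read next to the sentence before it, it appears to describe symptoms that have already passed the causal condition. It does not clearly widen the net.

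**Step 4. The time covered by the stated enquiry.** Two sessions a week for five weeks is 10 per participant, or 10 × 125 = 1,250 in all, of which 125 (10%) are last sessions. Those sessions span 5 weeks. With the final evaluation a year after treatment, total time is about 5 + 52 = 57 weeks, so the stated enquiry covers 5/57, or about 9%. Both figures describe coverage. Neither is a rate of missed events.

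**The case against.** The strongest reply is the masking. The control arm has real needling and a stimulator running on channels not connected to the patient. The placebo arm has electrodes attached to its needles. Patients are blinded until the 12-month evaluation is complete. A participant who believes the current is on can blame it for a symptom as readily as one who actually receives it. This stands, and it is why unequal attribution is a risk and not a shown effect. A reader might infer from the 75/50 split that the filter does act differently in the two sets of arms; the documents do not establish that. Nor do they establish equality. The plan itself leaves belief open by asking whether real electroacupuncture was felt. The answers could show that perception differed, but could not restore unrecorded symptoms.

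A second reply is that the article paraphrases the question, and that electroacupuncture may be loose shorthand for the study treatment. That is possible. Even so, the scope is stated, and it remains conditional on cause whichever treatment is meant.

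A third reply is that no safety comparison between arms is planned: the objectives concern efficacy, and adverse events are not a listed outcome. That is correct and limits the weight of the point. But a record of harms in a five-arm trial will naturally be read by arm.

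On timing, a reader might infer that adverse events are collected only at sessions and that later ones are lost. The documents do not support this. The article does not exclude later enquiry, the questionnaire has no stated timing, withdrawal reasons are recorded throughout, and a condensed article may leave follow-up collection to the full protocol. What can be said is narrower: no later enquiry is stated here, and a withdrawal record would not capture a symptom in someone who finished treatment and stayed in follow-up.

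**Conclusion.** The point holds for the scope of the question. As written, adverse event enquiry is conditional on an association with electroacupuncture in a trial where 50 of 125 participants receive no current. Symptoms are filtered by presumed cause before recording, and reporting may differ by arm if perceived treatment differs. The size is unknown. The illustrative 2.5 to 22.5 points assume equal true risks of 10% to 30% and reporting without current at 75% to 25% of the level with it; equal attribution gives zero. No sample size, power or error rate is affected.

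The timing point is secondary and provisional. The article names the treatment session as the only occasion for enquiry, so a reaction appearing after session 10 has no stated enquiry. Whether that is a gap depends on the full protocol.

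**What to change.** At each session, ask all five arms in identical words about any new or worsened symptom since the last contact, whatever its presumed cause. Record attribution to treatment as a separate item, after the symptom has been noted.

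Check the full protocol for enquiry after session 10. If none is planned, put the same question at the follow-up evaluations already scheduled. The post-treatment evaluation comes immediately after the last session and may catch few delayed reactions, so it should not be the only one.

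The cost is the rewording of one question, one added item for attribution and, if needed, the same question at existing evaluations. No visit is added. More unrelated symptoms will be recorded. The change concerns data collection only; the handling of severe symptoms is left as it is.
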